### CPR concealment

Hospitals randomised to the concealed arm will not base management on the CPR result. The CPR will be performed by a sonographer or other physician who is *not involved* in the participant’s treatment. The measurements made will be printed during the scan and will not be saved and thus not transferred to the data capture software program. Only after delivery the scan results can be completed in the data capture form. This ensures that the CPR result, as well as the pulsatility indices of the umbilical- and middle cerebral artery, are concealed for the treating clinician until after delivery.

### Participants and eligibility criteria

All women with a singleton pregnancy and perceived RFM with a gestational age from 37^+ 0^ up to and including 40^+ 6^ weeks, a fetus in cephalic presentation and normal cardiotocograph are eligible.

Exclusion criteria include:
Small for gestational age, defined as abdominal circumference < p10 based on the Verburg reference curve [23] and/or estimated fetal weight < p10 according to Hadlock 3 formula [24] on ultrasound;Planned caesarean delivery, except an elective repeat caesarean delivery;Abnormal (ultrasound) findings that indicate immediate need for delivery*;Planned delivery within 4 days of presentation with RFM;Major congenital malformations or chromosomal abnormalities that can influence pregnancy outcomes chosen for this study;Poorly controlled diabetes mellitus.

*This may for instance mean an absent or reversed end diastolic flow in the umbilical artery, depending on local protocol.

### Outcome measures

Primary outcome is a composite of severe neonatal outcome consisting of: stillbirth, neonatal mortality, Apgar score < 7 at 5 min, pH < 7.10 (umbilical artery), emergency delivery for fetal distress (need for cooling, caesarean section or ventouse/forceps) and severe neonatal morbidity (respiratory distress syndrome, hypoxic ischemic encephalopathy, sepsis, necrotizing enterocolitis and supplementary oxygen therapy (> 4 days)).

Secondary outcomes include:
Mild and other neonatal outcomes, including hypoglycaemia, hypothermia and admittance to neonatal ward.Long-term child outcomes including general health, development and behaviour. Child development and behaviour will be assessed 24 months postpartum using the validated Ages and Stages Questionnaire (ASQ-3) and Child Behaviour Checklist (CBCL/1.5–5).Maternal outcomes including health related quality of life, fear of childbirth, and development of hypertensive disorders of pregnancy. Wellbeing and fear and experience of childbirth are assessed using the validated questionnaires European Quality of Life 5-Dimension 5-Level (EQ-5D-5L), Wijma Delivery Expectancy/Experience Questionnaire (WDEQ-A and WDEQ-B) and posttraumatic stress disorder checklist for DSM-5 (PCL-5).Analysis of maternal serum markers (PlGF, sFLt-1, and PlGF/sFLt-1 ratio) in the context of normal and abnormal CPR and in relation to (adverse) outcomes and baseline characteristics.Analysis of the accuracy of routine placental immunohistochemistry.Cost-effectiveness analysis of monitoring-intervention strategy. A short-term and long-term cost-effectiveness analysis from a societal perspective will be performed as well as a budget impact analysis.

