### Sample size calculation

We estimate a reduction of the incidence of the composite adverse neonatal outcome from 12 to 8%. The background risk of 12% is extrapolated from the existing literature on RFM as applicable to our population [2, 21, 25–29]. This is an extrapolation because there has been heterogeneity in reported outcome measures in RFM studies. We anticipate an incidence of stillbirth and neonatal mortality (< 28 days) of 0.5%, and an incidence of Apgar score < 7 at 5 min and/or pH < 7.10 umbilical artery and/or emergency delivery for fetal distress of 11% (indicative for peripartum asphyxia). The less common events are grouped into severe neonatal morbidity and include: need for cooling, respiratory distress syndrome, hypoxic ischemic encephalopathy, sepsis, necrotizing enterocolitis and, supplementary oxygen therapy (> 4 days). For severe neonatal morbidity we anticipate an incidence of 1% of which 0.5% overlaps with peripartum asphyxia.

Based on these assumptions, a total of 2160 patients obtained from 24 clusters with 90 patients per cluster (equal numbers of control and intervention), achieve 80.06% power to detect a difference in the primary outcome from 12 to 8%, with an alpha of 5%, and an intra-cluster correlation of 0.002.

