### Interventions

After recruitment and consent, an ultrasound scan for fetal biometry, amniotic fluid volume, uterine artery pulsatility index and CPR is performed. The pulsatility indices of both the umbilical artery and middle cerebral artery will be reported aside from the calculated CPR. Depending on the cluster, clinicians will be either blinded or unblinded to the CPR. Expedited delivery is pursued in women with an abnormal CPR – defined as an CPR < 1.1 - in the open arm. In this case we aim to start delivery within 16 h or an elective caesarean section will be advanced. There are no criteria for discontinuing the intervention other than participant request. In this case she will be followed-up for intention-to-treat analysis. Women in the concealed arm will not have their CPR results revealed and will receive routine clinical care (Fig. 1).

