### Strengths and challenges

A strength of this proposed study is the large control group. The concealed arm (control group) is, however, a logistic challenge. Several options to conceal the CPR result have been explored. Concealing the CPR result at software- or ultrasound device level appeared to have many organisational (many systems available for both ultrasound machines and ultrasound data capture software) and legal limitations. Despite considerable efforts by ultrasound companies and ultrasound data capture software builders, this blinding method proved to be unfeasible. The current approach in which the CPR is concealed for the treating physician was considered to be a proper alternative and is extensively described in the methods section.

Another strength is the sampling of serum biomarkers. The predictive value of maternal biomarkers to detect placental insufficiency at term is currently unknown. In combination with the obtained Doppler results we hope to facilitate the first steps in developing an individualised prediction model to detect pregnancies at risk for placental insufficiency.

The cluster design was preferred over randomisation at the individual patient level because it was expected that both clinicians and the pregnant women would not be willing to wait for spontaneous delivery once an abnormal CPR is measured. Randomisation at cluster level was postulated to lead to a better implementation of the intervention in participating sites.

This cluster RCT will determine whether the CPR is an effective marker to guide management in pregnancies at term complicated with RFM. If the CPR proves to be an adequate indicator for delivery, expedited delivery will be restricted to the smaller number of compromised fetuses suffering from placental insufficiency, reducing their stillbirth risk and improving long-term health. Moreover, a larger group of women with perceived RFM can be reassured and monitored less intensively, reducing their burden of unnecessary intensified monitoring and interventions, resulting in substantial lowering of health costs.

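### The primary neonatal composite counts emergency delivery for fetal distress, a decision by clinicians who know the CPR in one arm only, so it can differ between arms with no change in any measure taken on the baby

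*Protocol article*

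**What the plan says.** The study objective (Protocol article, Study objective) is whether expedited delivery for a low CPR improves neonatal outcome. Under Outcome measures, the primary is labelled a composite of severe neonatal outcome. Besides death, 5-minute Apgar, umbilical artery pH and severe morbidity, it includes "emergency delivery for fetal distress (need for cooling, caesarean section or ventouse/forceps", closing the bracket there.

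Randomisation assigns each hospital to one arm for the whole study. Under Interventions: "Depending on the cluster, clinicians will be either blinded or unblinded to the CPR". CPR concealment adds that in concealed hospitals the result stays hidden from the treating clinician until after delivery.

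Sample size calculation gives one joint rate for low Apgar and/or low pH "and/or emergency delivery for fetal distress of 11% (indicative for peripartum asphyxia"), with no split between the three. It adds 0.5% for death and 1% for severe morbidity, half of which overlaps with the 11%. It also places cooling elsewhere than Outcome measures does: "The less common events are grouped into severe neonatal morbidity and include: need for cooling".

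**The concern.** Death, Apgar, cord pH and the listed morbidities describe the baby. A caesarean or instrumental delivery for fetal distress describes what the team decided and how they recorded the reason. Here the information available to the people deciding differs by arm, by design. A known normal CPR may make a clinician slower to call distress, and a known low CPR may make the clinician quicker. Either would change the primary outcome without changing any neonatal measure.

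The interpretation of the headline result is at stake. A significant primary would naturally be read as improved neonatal outcome, which is the stated objective, although it could arise from a change in mode of delivery. A shift the other way could hide a real neonatal benefit.

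**Working it through.** **Inputs from the article.** Composite 12% versus 8%; 24 clusters of 90, so 12 clusters and 1080 women per arm; ICC 0.002; alpha 5% (taken as two-sided); low CPR in about 6% of women with reduced fetal movements (Background).

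**Step 1: reproduce the plan's figures.** The plan has "a total of 2160 patients obtained from 24 clusters with 90 patients per cluster (equal numbers of control and intervention") and says these "achieve 80.06% power to detect a difference in the primary outcome from 12 to 8" per cent.
- Design effect: 1 + (90 − 1) × 0.002 = 1.178. Effective n per arm: 1080 / 1.178 = 916.8.
- Null SE: √(2 × 0.10 × 0.90 / 916.8) = 0.01401. Alternative SE: √((0.12 × 0.88 + 0.08 × 0.92) / 916.8) = 0.01398.
- Power: Φ((0.04 − 1.96 × 0.01401) / 0.01398) = Φ(0.897) = 81.5%, close to the stated 80.06%.
- Component sum: 0.5 + 11 + (1 − 0.5) = 12.0%, as stated.

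**Step 2: what is known about the component's share.** Let x be the percentage points of women whose only qualifying event is emergency delivery. The composite without it is 12 − x. Deaths (0.5) and severe morbidity (1) remain in it, so it is at least 1.5 and x can be at most 10.5. The article narrows x no further, so x is an assumption, shown from 3 to 10.

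**Step 3: a shift in threshold among women with a normal CPR.** Assume a 20% relative change in the component in the 94% with a normal CPR, and the same x in them as overall. The change in the composite is 0.94 × x × 0.20:
- x = 3: 0.56 points
- x = 5: 0.94 points
- x = 8: 1.50 points
- x = 10: 1.88 points

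That is 14% to 47% of the 4-point target (0.56 / 4 and 1.88 / 4). The smallest observed difference reaching p < 0.05 is about 2.8 points, so a shift of this size would not usually be significant alone. It would add to, or subtract from, any true effect.

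**Step 4: a larger fall in this component only.** All other components are held unchanged. The probability of a significant benefit uses the Step 1 formula with 12% against 12% minus the fall. With no difference it would be 2.5% in that direction. The last column is the power of the composite without emergency delivery at the planned size, for the planned relative risk of 8/12 = 0.667.

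| x | one-third fall in x | one-half fall in x | fall in x giving the full 4 points | power, restricted composite |
|---|---|---|---|---|
| 3 | 10% | 17% | not possible | 68% |
| 5 | 20% | 41% | 80% | 57% |
| 6 | 28% | 55% | 67% | 50% |
| 8 | 46% | 82% | 50% | 36% |
| 10 | 65% | 96% | 40% | 20% |

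**Step 5: why women with a normal CPR matter.** A 4-point drop is 0.04 × 1080 = 43 events per arm, while only 0.06 × 1080 = 65 women per arm have a low CPR. If only they benefited, 43 / 65, or two thirds, would need to have an event under concealment and all of those events would have to be prevented. At lower risks, part of a difference as large as planned has to come from the 94% with a normal CPR, for whom the open arm differs chiefly in that the clinician knows the result.

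**Step 6: cooling.** Outcome measures lists it inside emergency delivery; Sample size calculation lists it under severe morbidity. The primary counts it either way. A composite without emergency delivery keeps or loses it depending on which section is followed.

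**The case against.** Several stronger readings are tempting and do not hold.

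- **Emergency delivery is the largest part of the composite.** The article gives only a joint 11% for three components, two of them measured on the baby. The group is 11 of 12 points; the component's share is unknown.
- **The trial will show a false benefit.** The direction is not fixed, and producing the full 4 points from this component needs a 40% to 80% fall in it for x between 10 and 5. Smaller shares and shifts matter less: with x = 5 and a 10% shift, 0.94 × 5 × 0.10 = 0.47 points. A spurious difference is possible, not demonstrated.
- **The plan expects less monitoring of normal-CPR women during the trial.** The Discussion does say "a larger group of women with perceived RFM can be reassured and monitored less intensively", but on condition that the CPR proves adequate. It describes care after a positive trial. Interventions specifies a change of management only for a low CPR in the open arm.
- **The plan has no composite without this component.** The secondary outcomes are introduced as a non-exhaustive list, and an analysis plan that is not shown may contain one. Its absence cannot be asserted.

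It can also fairly be said that fewer emergency deliveries may be a genuine and welcome effect of the strategy. That stands, but it is an effect on mode of delivery, not the improvement in neonatal outcome named in the objective.

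None of this touches what the article itself fixes: the definition and label of the primary, and the difference between arms in what the deciding clinicians know.

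**Conclusion.** The point holds as a weakness in how the primary can be interpreted. A component decided by clinicians with arm-dependent knowledge sits in a composite called a severe neonatal outcome, within a group that makes up 11 of the 12 expected points. The composite can therefore move, in either direction, with no change in death, Apgar, cord pH or morbidity.

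The size depends on the unstated share x. A 20% shift in women with a normal CPR is worth about 0.6 to 1.9 points for x from 3 to 10. A one-third fall in the component alone gives a significant primary with probability of about 20% (x = 5) to 65% (x = 10). The share and both shifts are assumptions; the 6% prevalence, the 12% and 8% rates, the ICC and the sample size are the article's. The two placements of cooling conflict on the face of the text.

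**What to change.** Keep the registered primary. Pre-specify as a key secondary the same composite without emergency delivery: stillbirth, neonatal death, 5-minute Apgar below 7, umbilical artery pH below 7.10, and severe neonatal morbidity including cooling. Use the same model, and report it with its 95% CI beside the primary and the results for each component.

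State in advance that a difference carried only by emergency delivery will be described as a change in mode of delivery and not as improved neonatal condition. Do not make agreement in direction a pass/fail test: with no neonatal effect, it would be met about half the time by chance.

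Reconcile the two sections on need for cooling so that it counts in the restricted composite.

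The cost is one more analysis and a wording correction, using data already collected. The drawback is low power for the restricted composite: about 57% at x = 5 and 36% at x = 8 for the planned relative risk. Its interval will be wide, and a non-significant result must not be read as absence of neonatal effect.

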### Sample size calculation

We estimate a reduction of the incidence of the composite adverse neonatal outcome from 12 to 8%. The background risk of 12% is extrapolated from the existing literature on RFM as applicable to our population [2, 21, 25–29]. This is an extrapolation because there has been heterogeneity in reported outcome measures in RFM studies. We anticipate an incidence of stillbirth and neonatal mortality (< 28 days) of 0.5%, and an incidence of Apgar score < 7 at 5 min and/or pH < 7.10 umbilical artery and/or emergency delivery for fetal distress of 11% (indicative for peripartum asphyxia). The less common events are grouped into severe neonatal morbidity and include: need for cooling, respiratory distress syndrome, hypoxic ischemic encephalopathy, sepsis, necrotizing enterocolitis and, supplementary oxygen therapy (> 4 days). For severe neonatal morbidity we anticipate an incidence of 1% of which 0.5% overlaps with peripartum asphyxia.

Based on these assumptions, a total of 2160 patients obtained from 24 clusters with 90 patients per cluster (equal numbers of control and intervention), achieve 80.06% power to detect a difference in the primary outcome from 12 to 8%, with an alpha of 5%, and an intra-cluster correlation of 0.002.

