Stillbirth prediction is difficult and the fear of vital consequences leads to substantial overtreatment of women reporting RFM. Functional parameters, such as Doppler ultrasound and serum biomarkers, can help distinguish the compromised fetuses from healthy fetuses. A low cerebroplacental ratio (CPR) on Doppler ultrasound reflects a decrease in resistance in the middle cerebral artery (cerebral flow) and/or an increased resistance in the umbilical artery (placental flow) indicating redistribution of the fetal circulation: a compensatory adaptation to nutrient and oxygen deprivation due to placental insufficiency. A low CPR can identify a compromised fetus regardless of fetal size [6–9], and using the CPR combined with RFM may aid prediction and consequently prevention of stillbirth [10].

The incidence of an abnormal CPR in RFM is approximately 6% [4]. There are no studies of a management strategy based on an abnormal CPR for RFM. In a systematic review that included pregnancies of any risk profile, the CPR outperformed the umbilical artery pulsatility index in the prediction of emergency delivery for fetal distress and prediction of composite adverse outcome. A pooled sensitivity of 0.93 and specificity of 0.74 for perinatal death and a sensitivity of 0.59 and specificity of 0.91 for a composite adverse outcome was found for a CPR <5th centile (equivalent to CPR < 1.1), independent of birth weight [7, 11]. When analysing individual patient data from studies included in this systematic review, the CPR showed no added predictive value for adverse perinatal outcome beyond the umbilical artery pulsatility index, irrespective of gestational age or fetal size [12]. A possible explanation for this controversy could be that in the latter continuous data were used whereas in the review a cut off value was applied to determine (ab)normality.

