The aim of this cluster randomised trial is to compare outcomes in women presenting with RFM at term, randomised to either expectant management or immediate induction of labour based on a low CPR for gestation. We will compare neonatal and maternal outcomes, as well as the healthcare costs in both groups. We will also evaluate the predictive value of serum biomarkers (sFlt-1 and PlGF).

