## Methods

### Study objective

To assess whether expedited delivery (induction of delivery within 16 h) in pregnancies at term complicated with RFM and an abnormal CPR (< 1.1) improves neonatal outcome as compared to clinical management where the CPR remains concealed.

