## Statistical analysis

### Data analysis plan

The primary analysis will estimate the relative risk (RR) with 95% confidence intervals and *p*-values for the composite perinatal outcomes, using a generalized linear mixed model with log link and binomial distribution, with random intercepts and random slopes per cluster. The primary analysis will be performed according to the intention-to-treat principle. A per protocol analyses will be done as secondary analysis.

Dichotomous secondary outcomes will be analysed using the same method as the primary outcome. Continuous data of secondary outcomes will be assessed using a linear mixed model to estimate mean differences, with random intercepts and slopes as appropriate. Median differences will be calculated as appropriate. A significance level of 5% will be used for all tests. Interim testing for efficacy will not be performed, hence the significance level does not need to be lowered.

Given that all required data is collected for routine patient care in both primary and secondary care, missing data is expected to be limited. Multiple imputation will be used if required.

Data of quality of life measures will be obtained at four time points and will be analysed using generalised estimating equations.

For subgroup analyses we will assess the relationship between pregnancy characteristics, outcomes and abnormal serum biomarkers of PlGF and sFlt-1.

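### The 12% to 8% effect is averaged over all women, but expedited delivery reaches only the roughly 6% with a low CPR, so the stated 80% power says little about the objective as worded

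*Protocol article*

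**What the plan says.** The Study objective asks whether expedited delivery "in pregnancies at term complicated with RFM and an abnormal CPR (< 1.1) improves neonatal outcome" compared with management in which the CPR stays concealed. The aim at the end of the Background describes women "randomised to either expectant management or immediate induction of labour based on a low CPR for gestation". Both are worded around women with a low CPR.

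The design is wider. Participants and eligibility criteria contains no CPR criterion. Under Interventions, CPR is measured after consent, and expedited delivery is pursued only in open-arm women with CPR below 1.1. Women in concealed hospitals receive routine care.

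The Sample size calculation is for everyone enrolled. Its effect is "We estimate a reduction of the incidence of the composite adverse neonatal outcome from 12 to 8" percent, and "The background risk of 12% is extrapolated from the existing literature on RFM as applicable to our population", meaning women with RFM in general. The total is "a total of 2160 patients obtained from 24 clusters with 90 patients per cluster (equal numbers of control and intervention"), said to "achieve 80.06% power to detect a difference in the primary outcome from 12 to 8%, with an alpha of 5%, and an intra-cluster correlation of" (the value used is 0.002). The Data analysis plan adds that "The primary analysis will be performed according to the intention-to-treat principle", with no restriction by CPR. It also names a per-protocol analysis and biomarker subgroup analyses.

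The Background gives the share of women who can be directed to the intervention: "The incidence of an abnormal CPR in RFM is approximately 6% [4"].

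**The concern.** The population in the objective is a small part of the population that is powered and analysed. About 94% of women have a normal CPR, and the protocol directs no difference in their delivery. The 8% is not derived from the low-CPR share or from the risk in low-CPR women, so a reader cannot see how treating about 6% of women would lower the risk of all women by a third.

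If the benefit lies where the intervention acts, the primary test could easily be null even when expedited delivery halves the risk in its target group. That null could then be reported as evidence that CPR-guided delivery does not work, a question the all-women test would have had little power to answer.

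**Working it through.** **Inputs from the article.** Risks 12% and 8%; 24 hospitals of 90 women, 1080 per arm; alpha 5% (taken as two-sided); intra-cluster correlation 0.002; low-CPR share about 6%; sensitivity 0.59 and specificity 0.91 for a composite outcome (Background). **Assumed, because the article does not give it:** the risk in low-CPR women under concealed care, varied from 20% to 50%.

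**1. The stated power.** Design effect 1 + 89 × 0.002 = 1.178. Effective size per arm 1080/1.178 = 916.8. SE of the difference √[(0.12×0.88 + 0.08×0.92)/916.8] = 0.0140. Power is 81.5% by a normal approximation and 78.1% by a t-test with 22 df (24 hospitals minus 2), against 80.06% stated. The arithmetic is sound; the question is the effect-size input.

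**2. Reduction needed in low-CPR women.** With no effect in normal-CPR women, overall reduction = share × reduction in low-CPR women.
- 6% share: 0.04/0.06 = 66.7 points
- 10% share: 0.04/0.10 = 40 points
- 15% share: 0.04/0.15 = 26.7 points

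At 6%, the low-CPR risk would have to be at least 66.7%, with every event prevented at that value.

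**3. Power at a 6% share, low-CPR risk halved** (t-test, 22 df). Low-CPR women number 0.06 × 2160 ≈ 130: 64.8 per arm, 5.4 per hospital, design effect 1 + 4.4 × 0.002 = 1.009.

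| Low-CPR risk | Overall risk | Power, all women | Power, CPR < 1.1 only |
|---|---|---|---|
| 20% → 10% | 12.0% → 11.4% | 7% | 33.5% |
| 30% → 15% | 12.0% → 11.1% | 9% | 51% |
| 40% → 20% | 12.0% → 10.8% | 12% | 68% |
| 50% → 25% | 12.0% → 10.5% | 16% | 83% |

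If every low-CPR event were prevented, all-women power would be 22% at 30% risk (overall fall 0.06 × 30 = 1.8 points) and 52% at 50% risk (3.0 points).

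**4. Larger shares.** Halving a 50% risk gives 12.0% to 9.5% and 38% power at a 10% share, and 12.0% to 8.25% and 72% power at a 15% share.

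**5. The article's accuracy figures.** At 12% risk, women flagged = 0.59×0.12 + 0.09×0.88 = 0.0708 + 0.0792 = 15.0%, with an event risk of 0.0708/0.150 = 47.2%. Preventing half of those events gives 12.0% − 3.54 = 8.46%, with power about 67%. A 4-point fall would need 0.04/0.0708 = 56% of them prevented. The 15% does not agree with 6%: if only 6% are flagged, at most 0.06/0.12 = 50% of events can fall among them, below the quoted sensitivity of 0.59.

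**6. Precision in low-CPR women.** At 30% versus 15%, the SE of log RR is √[(0.7/0.3 + 0.85/0.15)/64.8] = 0.351. With the t multiplier 2.074, RR 0.50 has a 95% interval of about 0.24 to 1.04.

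**The case against.** The strongest reply is that this is a strategy trial: hospitals are randomised to reveal or conceal the CPR, so all women are the right primary population. Under Strengths and challenges, the article expects that women with a normal CPR can be reassured and monitored less. The composite includes emergency delivery for fetal distress, a clinical decision that knowing the CPR could alter in any open-arm woman. This stands as a defence of the primary analysis. It does not justify 4 points, because no neonatal gain in normal-CPR women is quantified.

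A second reply is that the 6% is approximate and cited, and that the trial's own share may differ. This also stands. A reader might infer that the article's accuracy figures give the planned effect no support, but they come close to it (step 5). It is the 6% that conflicts with them. Those accuracy figures come from pregnancies of any risk profile, so neither input is established for this population.

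Third, a separate analysis plan may define a low-CPR comparison. That comparison is therefore absent only from the analyses this article names, and nothing here shows that it is absent from the trial.

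Finally, membership of the low-CPR group could differ by arm. CPR is measured after consent in hospitals whose allocation is fixed. Open-arm clinicians see a result that triggers delivery, while concealed-arm values are printed and entered only after delivery. Repeat measurement near 1.1 or missing entries could unbalance the groups. This calls for a safeguard but does not rule the comparison out.

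**Conclusion.** The point holds. The objective concerns women with CPR below 1.1, whereas the sample size and primary analysis concern all 2160. At the article's own 6% share, and with no effect in normal-CPR women, the planned difference needs a 66.7-point absolute reduction in about 65 women per arm. Halving assumed low-CPR risks of 20% to 50% leaves about 7% to 16% power in all women. The 80% is approached only with a much larger flagged share (about 67% power with 15% flagged and half their events prevented) or with unquantified benefit in normal-CPR women.

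A reader might go further and infer that a positive result must come mostly from normal-CPR women. That does not follow. An observed difference of about 3 points is significant (2.074 × 0.0143 ≈ 0.030), preventing every event at a 50% low-CPR risk would yield 3 points from low-CPR women alone, and chance can also produce a positive result.

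**What to change.** - Keep the all-women intention-to-treat analysis as the test of the reveal-CPR strategy, and word the Study objective to match it.
- In the Sample size calculation, state that about 80% power applies to a 4-point reduction averaged over all women. Give power over a range of low-CPR shares and risks, and reconcile the 6% with the quoted sensitivity and specificity.
- Pre-specify an intention-to-treat comparison of open versus concealed hospitals among women whose first recorded CPR is below 1.1, with an arm-by-CPR interaction. Report it as an estimate with its interval.
- Do not gate this comparison behind the primary test. A gated test cannot have more power than its gate, which is 7% to 16% in the scenarios above.
- Report by arm the proportion with CPR below 1.1 and the completeness of CPR recording, as a check that the groups are comparable.
- State in advance that a null all-women result will not be read as showing that expedited delivery for low CPR is ineffective.

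The cost is wording, since CPR is already measured in both arms. The drawback is imprecision: about 130 women give a wide interval, as in step 6, and the comparison may not be conclusive by itself.
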